### Health economic evaluation

A within-trial cost-utility analysis will be undertaken to assess the cost-effectiveness of the intervention compared with standard care. The perspective will be that of the National Health Service and Personal Social Service as recommended by the National Institute for Health and Care Excellence [37]. The outcome of the cost-utility analysis will be the cost per quality-adjusted life year (QALY) gained. QALYs will be calculated using utilities generated from responses on the EuroQol 5 dimension questionnaire 5 level version administered over the study period. Healthcare resource use over the study period will be collected using a questionnaire administered at 6 months post-randomisation. Overheads, capital and patient training costs will be determined based on an average exercise class. Intervention costs will also be captured and will include the costs associated with staff training and delivery of the intervention. Unit costs will be applied from published national sources such as the National Health Service Reference Costs [38], British National Formulary, and the Unit Costs of Health and Social Care [39]. An incremental cost effectiveness ratio will be calculated to estimate the cost per QALY gained. Patient level cost and QALY data will be bootstrapped and a cost-effectiveness acceptability curve will be derived to show the probability of the intervention being cost-effective compared to usual care at various thresholds of willingness-to-pay for an additional QALY. Sensitivity analysis will be performed to explore the impact on cost-effectiveness of variations in key parameters. Costs which might be borne by the patient will also be explored. Given the study timeframe, discounting will not be necessary.

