### Recruitment

Patients in the ICUs will be prospectively screened. All eligible consecutive patients will be given written information about the study following discharge from critical care. They will be approached to enquire if they are interested and willing to take part in the study. A screening log of all non-recruited patients and the reason for exclusion will be maintained. If willing to participate, patients will be asked to provide written informed consent by a trained member of the research team prior to commencing the study. Participants will be randomised to the exercise programme or standard care. A randomisation schedule will be produced using permuted block randomisation technique, at a 1:1 ratio. Variable block sizes are used to ensure blinding. The randomisation schedule will be generated using nQuery Advisor by the clinical trials unit (NICTU). Allocations are done centrally by the NICTU (allocation concealment). The randomisation service will allocate a unique trial identification number to each participant in accordance with the computer-generated study randomisation schedule. In order to maintain confidentiality, all case report forms, study reports and all communication regarding the study will identify participants using the unique identification numbers. Participants allocated to the programme of exercise will commence as soon as possible.

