### Sample size

There is limited data available in this specific research area in order to conduct a formal sample size calculation. Jones and colleagues [11] demonstrated an approximate 24% improvement in the physical function score of the SF-36 with a rehabilitation manual which included a self-directed exercise programme. With the limited data available we have used a more general method to calculate the sample size [18], which would result in 52 patients (26 per group) for a large effect size. On the basis of our previous experience and published data we have estimated a loss of 25% after randomisation [19]. Thus, this study will aim to recruit up to 68 patients (34 in each group), or until we achieve 52 (26 per group) completed datasets at 6 weeks over the proposed 36-month recruitment period. Participants will be withdrawn on request, if there are adverse effects arising from the exercise programme, or due to inability to perform baseline assessment.

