### Data collection

Blinded outcome assessment will be conducted at baseline within two weeks of hospital discharge or when the patient is deemed medically stable (or in exceptional circumstances this will take place immediately prior to hospital discharge), following the exercise intervention, and at 6 months (24 weeks) following baseline assessment (or equivalent time points for the standard care group). These will be conducted by trained independent assessors blinded to group allocation. Informed consent will be obtained from each participant. Following consent and randomisation, the following will be recorded: demographics, ICU diagnosis and any co-morbidity and illness severity using acute physiology and chronic health evaluation II score.

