### Outcome measures

The primary outcome measure is physical function as measured by the physical functioning subscale of the SF-36 following the exercise programme. This has been shown to be an acceptable, reliable and valid tool following critical illness [25].

Several secondary outcomes will be evaluated to determine whether an exercise programme can improve these important clinical outcomes. These outcome measures will assess physical function, health-related quality of life, exercise capacity, anxiety and depression and self-efficacy to exercise in these participants. Healthcare resource use will also be evaluated [25-35] (Table 1).

**Table 1 T1:** Secondary outcome measures

**Outcome measure**	**Instrument**
Physical function	Rivermead Mobility Index [26]
Hand function (strength and dexterity)	Dynamometry [27]
	Nine Hole Peg Test [28]
Exercise capacity	Incremental Shuttle Walk Test [29]
Health-related quality of life	Other subscales of the Short-Form-36 Health Survey (role limitations due to physical health, bodily pain, general health perceptions, vitality, social functioning, role limitations due to emotional problems, and mental health) [25]
	Functional Limitations Profile [30]
	EuroQol 5 dimension questionnaire 5 level version [31]
Breathlessness	Medical Research Council Dyspnoea Scale [32]
Anxiety and depression	Hospital Anxiety and Depression Scale [33]
Readiness to exercise	Readiness to Change Questionnaire [34]
Self efficacy to exercise	Chronic Disease Self Efficacy Scale [35]
Healthcare resource use	Resource use questionnaire

Feasibility (safety, practicality and acceptability) of providing the exercise programme will also be assessed by the occurrence of adverse events, and recording information relating to recruitment and retention, and any difficulties with attendance and transport. Information regarding ease of execution of the exercise programme and the outcome measures will also be recorded.

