### Statistical methods/analyses

For continuously distributed outcomes, differences between groups will be tested using independent samples *t*-tests, analysis of variance and analysis of covariance with transformations of variables to normality if appropriate, or non-parametric equivalents. Chi-square tests (or Fisher’s Exact tests) will be used for categorical variables. Efficacy of intervention will be analysed on an intention-to-treat basis. A *P* value ≤0.05 will be considered significant. A single final analysis is planned at the end of the trial. Baseline variables will be recorded to demonstrate that the groups are comparable; if this is not demonstrated, *post-hoc* adjustments to correct for differences will be applied. Every effort will be made to collect outcomes from patients, even those who drop out of the exercise programme. Every effort will be made to minimise missing baseline and outcome data in this trial. The level and pattern of the missing data in the baseline variables and outcomes will be established by forming appropriate tables and the likely causes of any missingness will be investigated. This information will be used to determine whether the level and type of missing data has the potential to introduce bias into the analysis results for the proposed statistical methods, or substantially reduce the precision of estimates related to treatment effects. If necessary, these issues will be dealt with using multiple imputation or Bayesian methods for missing data as appropriate. The power calculations and methodology for data analysis have been reviewed and confirmed by the study statistician. Until data analysis is completed the study statistician will be unaware of whether the participant received the intervention or standard care.

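### The economic analysis states no adjustment for baseline EQ-5D utility, leaving the incremental QALY either raw or adjusted only after the data are seen, which costs precision in about 52 patients

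*Protocol article*

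**What the plan says.** The Health economic evaluation section plans a within-trial cost-utility analysis. EQ-5D-5L responses gathered during the study give utilities, utilities give QALYs, and costs and QALYs give an incremental cost-effectiveness ratio. For uncertainty it says: "Patient level cost and QALY data will be bootstrapped and a cost-effectiveness acceptability curve will be derived". Baseline utility is given no role as a covariate. The section says neither that the comparison is adjusted nor that it is unadjusted.

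EQ-5D-5L is listed in Table 1 under Outcome measures. Data collection places outcome assessment at baseline, after the exercise programme, and "at 6 months (24 weeks) following baseline assessment". The baseline value should therefore be available.

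Two statements under Statistical methods/analyses bear on the point. Analysis of covariance appears in a list of possible methods for continuous outcomes, with no covariate named. Separately, if baseline comparability is not shown, a post-hoc correction is promised. Neither statement mentions EQ-5D or the economic analysis. The Recruitment section describes a "permuted block randomisation technique, at a 1:1 ratio" and names no stratification factor.

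**The concern.** A QALY computed as the area under the utility curve contains the baseline utility directly, and is also correlated with it through the later utilities. Any chance difference between arms at baseline therefore passes into the incremental QALY unless it is adjusted for.

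On the text as written there are two possibilities. If the post-hoc rule does not reach the economic analysis, no adjustment is planned. If it does, adjustment depends on an inspection of the observed data, with covariates chosen afterwards. A comparability check is also a poor trigger. A baseline difference of one standard error has a two-sided P of about 0.32 and would pass as unremarkable, yet it still moves the QALY difference.

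The denominator of the cost-effectiveness ratio is at stake. In a small trial followed for 24 weeks it is likely to be a small number, so noise that could be removed matters to the reported ratio. Cost-effectiveness is part of the stated aim and is objective (v).

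**Working it through.** **The plan's own figure.** The article gives no utility SD, correlation or expected QALY gain. The figure to reproduce is the sample size, "which would result in 52 patients (26 per group) for a large effect size". Assuming a standardised difference of 0.8, two-sided 5% and 80% power (the article states neither sidedness nor power), the noncentral t gives 79.1% power with 25 per arm and 80.7% with 26. So 26 per arm is confirmed. With 25% loss, 68 recruits leave 68 × 0.75 = 51, one short of 52 and immaterial here. The 26 per arm refers to complete data at 6 weeks; further loss by 24 weeks would widen the figures below.

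**Assumptions.** Utility SD 0.20 to 0.30, the same at each visit; equal correlation r of 0.3 to 0.7 between visits; QALYs by the trapezoidal area under the curve at 0, 6 and 24 weeks. The article does not state the area rule.

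**Area weights (years).** Baseline 3/52 = 0.058; week 6 (6 + 18)/2 ÷ 52 = 12/52 = 0.231; week 24 9/52 = 0.173. The two later weights sum to 21/52 = 0.404.

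**Baseline imbalance.** SE = SD × √(2/26) = SD × 0.277.

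**Carry-over.** Expected QALY shift per unit of baseline difference = 3/52 + r × 21/52, which is 0.179, 0.260 and 0.340 for r = 0.3, 0.5 and 0.7. A one-SE imbalance then gives:

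| SD | SE of baseline difference | shift, r = 0.3 | shift, r = 0.5 | shift, r = 0.7 |
|---|---|---|---|---|
| 0.20 | 0.055 | 0.010 | 0.014 | 0.019 |
| 0.25 | 0.069 | 0.012 | 0.018 | 0.024 |
| 0.30 | 0.083 | 0.015 | 0.022 | 0.028 |

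**Comparison with a treatment gain.** A utility gain g, rising linearly to week 6 and held to week 24, is worth g × 21/52 QALY: 0.020 for 0.05, 0.040 for 0.10 and 0.061 for 0.15.

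**How often imbalance alone exceeds the gain in size.** P = 2 × [1 − Φ(gain in QALY ÷ (carry-over × SE))]. At SD 0.25 and r = 0.5 the divisor is 0.018.

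- Gain 0.05: 26% (4% to 48% over SD 0.20 to 0.30 and r 0.3 to 0.7)
- Gain 0.10: 2.5% (0% to 15%)
- Gain 0.15: 0.1% (0% to 3%)

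**What adjustment saves.** Let w be the weights. The variance of a patient's QALY is SD² × [(1 − r)Σw² + r(Σw)²], with Σw² = 0.0865 and (Σw)² = 0.2130. The share explained by baseline is R² = carry-over² ÷ the bracketed term, and the SE is multiplied by √(1 − R²).

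- r = 0.3: R² = 0.0320/0.1245 = 0.257; SE × 0.862, a 14% cut
- r = 0.5: R² = 0.0674/0.1498 = 0.450; SE × 0.742, a 26% cut
- r = 0.7: R² = 0.1159/0.1751 = 0.662; SE × 0.582, a 42% cut

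At SD 0.25 and r = 0.5 the SE of the QALY difference falls from 0.0268 to 0.0199. The variance ratio is (0.0268/0.0199)² = 1.8, so on QALYs an unadjusted analysis would need roughly 80% more patients for the same precision.

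**The case against.** The strongest reply is that the article has not chosen an unadjusted analysis. A bootstrap expresses uncertainty and works equally well around a regression-adjusted estimate, so the proposed remedy fits the published wording. An article condenses a fuller plan, and the covariates for incremental QALYs are the kind of detail left to a health economics plan that is not shown. This largely stands. A reader might infer that the trial has decided against adjustment; the documents do not say so. What remains is that the only baseline rule the article does state is triggered by the data, and that is a poor default for a variable known in advance to be prognostic for the QALY.

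A reader might also infer that the cost-effectiveness result will be biased. It will not be on average: under randomisation the raw QALY difference is unbiased, and the bootstrap spread already includes chance baseline imbalance. The acceptability curve would reflect more uncertainty than necessary, but would not be invalid for that reason.

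Finally, a reader might conclude that imbalance could match any plausible QALY gain. The figures do not support that. A sustained gain of 0.15 is exceeded at most about 3% of the time over the assumed range. For a gain of 0.8 SD, the size assumed for the large effect behind the sample size, the chance is below 0.1%. That effect size concerns the primary outcome rather than EQ-5D, but nothing in the article makes 0.05 a ceiling.

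**Conclusion.** The point holds as one about precision and pre-specification. As published, the economic analysis gives baseline utility no role as a covariate, and the nearest rule is a post-hoc one that may not apply to it. The consequences are a wider QALY comparison than necessary and a realised point estimate that chance imbalance can noticeably shift when the true gain is modest, around 0.02 to 0.04 QALY over 24 weeks. The sizes rest on assumed SDs, correlations and the area rule, since the article supplies none of these. That adjustment improves precision does not depend on their exact values, provided baseline and later utilities are positively correlated. The cost-utility analysis is not the trial's primary analysis, and the matter falls away if the health economics plan already specifies the adjustment.

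**What to change.** State in advance that incremental QALYs are estimated by regressing each patient's QALY on randomised group and baseline EQ-5D utility, whether or not imbalance is seen. Fit the regression within each bootstrap replicate, resampling patients within arm so that each patient's cost, QALY and baseline utility stay together. Build the ratio and the acceptability curve from those replicates, and report the unadjusted result as a sensitivity analysis. If the health economics plan already says this, it is enough to confirm it and to make clear that the post-hoc rule under Statistical methods/analyses does not govern the economic analysis. The cost is a change of analysis wording, with no new data, visits or patients.

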### Study quality and monitoring procedures

Rigorous study conduct and monitoring procedures will be put in place to ensure the research quality and data is of a high standard and to ensure any problems are identified and managed.

A Data Monitoring and Ethics Committee (DMEC) has been appointed to the study. The DMEC is independent of the study organisers. They will independently review cumulative safety data to determine whether the trial should continue as originally designed, should be changed, or should be terminated based on these data. Following each DMEC meeting, the DMEC Chair will provide written information of any recommendations related to continuing, changing, or terminating the trial to the principal investigator. The recommendations will be shared with the sponsor and the Research Ethics Committee.

An electronic case report form has been developed for the study by the NICTU, including validation checks to minimise missing data and errors. Outcome measures and other key data will also be monitored by an independent data monitor for any errors, missing data or inconsistencies.

Formal monitoring of study procedures at each site will take place at least once per year over the course of the study and as required thereafter. Regular review of training needs and training updates as required will be completed with the researchers carrying out the study procedures.

The study is sponsored by the University of Ulster and the Belfast Health and Social Care Trust whose role includes ensuring that good practice arrangements are maintained for the duration of the study in relation to the conduct of the study, monitoring and reporting. Participant safety and well-being will be protected by implementing standard operating procedures as set out in the Research Governance Framework, including the reporting and recording of adverse events. The study participants are covered by indemnity for negligent harm through the standard sponsor indemnity arrangements.

The usual regulations will be followed for communicating important protocol modifications to the sponsors, Research Ethics Committee and governing sites as appropriate and the trial registries will be updated accordingly.

In order to support translation of our results to clinical practice we will disseminate the findings of this study to relevant health professionals through conference presentation and publication in peer-reviewed journals. Authorship eligibility guidelines will be followed. Furthermore, we will provide information for the public via appropriate forums. Trial participants will be informed that they will be sent a summary of the results on request.

## Discussion

Survivors of critical illness have persistent reduced physical function and health-related quality of life, and ongoing healthcare utilisation. There is also significant negative impact in terms of economic, social, physical and psychological factors on those who care for survivors of critical illness following their discharge home [40]. The desired outcome following critical illness is the return to physical function and quality of life levels similar to those experienced before the critical illness.

This multicentre prospective phase II, allocation-concealed, assessor-blinded, randomised controlled clinical trial will investigate the effectiveness of a programme of exercise on physical function in patients discharged from hospital following critical illness compared to standard care. There is limited research exploring the effects of rehabilitation after discharge from hospital following critical illness and so this study will advance the knowledge and research in this area. Additionally it includes some design elements in the inclusion criteria, methodology, intervention and outcome assessments which are not included in other studies and will provide further added value. We aim to recruit patients who have had a longer time on mechanical ventilation in ICU than in previous studies (greater than 96 hours) so that the population are at higher risk of longer term sequelae after critical illness and therefore more likely to represent the population that would benefit most from rehabilitation interventions. By following the principles for the prescription of exercise outlined by the American College of Sports Medicine and professional bodies [20-23], the proposed intervention seeks to be as effective as possible in order to improve outcomes for these patients. Two out of three exercise sessions per week, for a 6-week period, will be supervised. Although standardised, the programme of exercise will be tailored and progressed to the capability of each individual. The structured and self-directed exercise manual will be included to support the intervention [7], and a consultation at the final exercise session relating to continuing exercise.

If effective, this study will improve outcomes that are meaningful to patients and their families, and inform the design of a future multicentre phase III clinical trial of exercise following recovery from critical illness. It will provide useful information which will help the development of services for patients after critical illness.

## Trial status

Recruitment is currently active in five recruitment sites [17] and the first patient was randomised in January 2012. It is anticipated that study accrual will be completed by December 2014.

## Abbreviations

6MWT: six-minute walk test; DMEC: Data Monitoring and Ethics Committee; NICTU: Northern Ireland Clinical Trials Unit; QALY: quality-adjusted life year; SF-36: Short-Form-36 Health Survey.
